## **Backgrounds and Objectives:**

Coronaviruses are a large family of viruses and a subset of coronaviridae that have been seven generations of this family have been discovered [1, 2]. This virus family was first introduced in 1965 which is most spread in mammals [2]. SARS-CoV2 is the last generation of this virus family, which was first discovered in 2019 in Wuhan, China. [3] This virus is classified as a Positive-strand RNA virus [2]. Most prevalent symptoms of this infection include headache, fever, dry cough, fatigue, maldigestion, and shortness of breath [4]. The incubation period varies from 2 to 14 days depending on the underlying diseases such as diabetes, hypertension, chronic obstructive pulmonary disease, cardiovascular and kidney disease, and the immune system function [5]. The severity of symptoms is individualized and varies from mild to inflammatory and fatal conditions. The mild type of this disease is known as the absence of pneumonia, but severe type respiratory, hypoxia and organ failure are more pronounced in severe and fatal types. Organ function or organ failure is seen [1]. The main transmission route of covid-19 is thorough respiratory droplets and close contact. RT-PCR is the most accurate diagnostic test, but CT scan and blood test can also be used [2, 5, 7, 8]. Previous studies have demonstrated that a number of people with the severe type of Covid-19 display symptoms of cytokine syndrome. This disorder which is often caused by overactive immune system, is a hyper inflammatory syndrome known as sudden and fatal hypercytokinemia and multiple organ failure (MOF) [9, 10]. The main mechanism of pathogenesis is the binding of the virus to angiotensin 2 receptors, which increases the activity of T lymphocytes and thus increases the production of inflammatory factors [1]. According to the above-mentioned statement, it seems that people whom boost their immune system, with the help of drugs, supplements and foods have been able to prevent the progression of inflammatory processes and overcome the disease [1, 2]. Therefore, immune boosting foods such as pomegranate could be considered as a potential therapeutic option [1-3, 11]. Pomegranate is a fruit with numerous antiviral and antioxidant compounds, including: polyphenols, flavonoids, tannins, anthocyanins and flavonoids, vitamins E and C, magnesium, zinc, potassium, iron and quercetin, whose beneficial effects on the various diseases including cardiovascular diseases and diabetes have been studied and have an enormous capacity to neutralize free radicals mainly because of ellagic acid and pomegranate collagen [12-16] [16-19]. As reported by Feng et al. these polyphenols have an inhibitory effect on NF- $\kappa$ B pathway which has a pivotal role in disease pathogenesis [18]. Reducing CRP and inhibiting the cytokine storm

pathway through the inhibitory effects of conjugated terpenes on PPAR factors is the other protective mechanisms [15, 20]. As far as our knowledge goes, this work is the first study which examines the anti-inflammatory effects of whole pomegranate juice on disease progression in covid-19 patients.

## **Material and Methods:**

### **Participants & recruitment:**

Out of the total number of hospitalized patients, 48 patients with definitive diagnosis based on PCR test, who also have other inclusion criteria, are included in the study by availability sampling.

### **Study Design & randomization:**

The present study will be performed as a Randomized, Placebo-Controlled, Double-Blind, Parallel-Group clinical trial on patients with Covid-19 admitted to Shahid Jalil Hospital in Yasuj (Kohgiluyeh & Boyr Ahmad province, south-west of Iran). The study protocol was approved by the Ethics Committee of the School of Nutrition and Public Health ( ) in Yasuj University of Medical Sciences and is in agreement with the declaration of Helsinki of the world medical association. This study was also registered in the Iranian Center for Clinical Trials ( ). Patients will be randomly divided into two groups of intervention (n=24), and placebo (n=24), by block random sampling method, which randomizes participants into 4 different blocks in each group, based on gender and age . Intervention group receive 500 ml of natural whole pomegranate juice twice a day, after lunch and dinner and control group receive the same amount of placebo with the same color and taste as natural juice. The pomegranate juice and placebo will be administered to patients by two nurses in opposite shifts. Patients will be followed for 14 days and the objectives of the study will be fully explained to the patient and their companions. An informed written consent form will be also obtained.

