***Exclusion criteria***

- Transfer of patients to the intensive care unit

- Death
- Unwillingness to continue participating in the study

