### **Clinical, Para clinical and dietary intake assessments:**

A demographic questionnaire containing information about age, sex, habitat, education, occupation etc., will be taken from patients. Medical history and medications/supplements history will also be asked of the patient or his companion.

Height, weight and waist to hip ratio (WHR) will be measured by standard methods [1] as well as the body mass index (division of weight in kilograms to the height in meters squared).

For the purpose of evaluating detailed information about nutrient intake and the food pattern, a 24-hour dietary recall for 3 days (including a weekend day) will be taken by a well-trained interviewer. Dietary intakes will be entered into Nutritionist IV software for further analysis.

10 cc blood samples will be obtained after 12 hour overnight fasting to measure complete blood count (CBC) and inflammatory indices including CRP, ESR & IL-6, at the baseline and by the end of week-2. In the case of patient discharge earlier than scheduled, they will be followed up after discharge and receive pomegranate juice or placebo. The length of hospital stay, disease complications, drug and prescription dosing and mortality rate will be recorded on a daily basis. If the patient refuses to continue the study for any reason, blood sample will be drawn on the same day.

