## **Study objectives:**

### ***Primary objectives***

To assess of the effect of Punica granatum juice on inflammatory biomarkers and CBC in patients with Covid-19

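### Allocation is balanced on gender and age only and the stated arm comparison is unadjusted, so at 24 per arm a chance gap in severity or baseline inflammation goes uncorrected

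*Protocol*

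**What the plan says.** Protocol, Study Design & randomization: two arms of 24, allocated by a block method "which randomizes participants into 4 different blocks in each group, based on gender and age". Severity is not a factor.

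Protocol, Participants & recruitment: 48 hospitalised, PCR-positive patients "are included in the study by availability sampling". Neither the inclusion nor the non-inclusion criteria set a COVID-19 severity band. The Exclusion criteria end participation on events that include "Transfer of patients to the intensive care unit".

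Protocol, Backgrounds and Objectives: "The severity of symptoms is individualized and varies from mild to inflammatory and fatal conditions", and "a number of people with the severe type of Covid-19 display symptoms of cytokine syndrome".

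Protocol, Primary objectives: "To assess of the effect of Punica granatum juice on inflammatory biomarkers and CBC in patients with Covid-19".

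Protocol, Clinical, Para clinical and dietary intake assessments: a blood count is taken together with "inflammatory indices including CRP, ESR & IL-6, at the baseline and by the end of week-2". The section lists no direct measure of severity at entry, such as oxygen need.

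Protocol, Data analysis: arms are compared by the independent t test or the Mann-Whitney test. No baseline value, randomisation factor or other covariate is named.

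**The concern.** The protocol's own background connects severe disease with an inflammatory syndrome, and its primary outcomes are inflammatory markers and blood counts. A patient's severity at entry is thus a plausible source of variation in the outcome. Neither the allocation nor the stated comparison takes account of it.

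With 24 per arm, moderate gaps in severity between arms are common by chance. A gap running one way can resemble a juice effect, and one running the other way can hide it. The stated test also ignores baseline values that the trial will already have collected, which wastes precision in a small trial.

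**Working it through.** **Inputs from the protocol.** 24 per arm, 1:1; significance at 0.05 (taken as two-sided); allocation on gender and age; markers measured at baseline and at the end of week 2; unadjusted arm comparison. The protocol gives no effect size, SD or power, so it has no figure of its own to reproduce.

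**Assumptions, since the protocol gives no figures.** Number severe K between 10 and 24 of 48; severe patients higher by d = 0.5, 1.0 or 1.5 SD, the SD being that within a severity class; correlation r between baseline and week 2 within a class of 0.3 to 0.7; severity shifts baseline and week 2 equally.

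**1. Chance of a gap.** If allocation ignores severity, the number of severe patients in one arm is hypergeometric (48, K, 24). With k severe in one arm, the gap is |2k − K|.

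| K severe | gap ≥ 4 | gap ≥ 6 |
|---|---|---|
| 10 | 29% | 7% |
| 14 | 34% | 11% |
| 24 | 39% | 15% |

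All even K from 10 to 24 fall within these ranges. With an odd K the gap is odd, so the thresholds become 5 and 7, and the chances are 17–25% and 4–8%.

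**2. Shift in the contrast.** Shift = gap/24 × d. At d = 1, a gap of 4 gives 4/24 = 0.17 SD and a gap of 6 gives 6/24 = 0.25 SD.

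**3. Yardstick.** 95% half-width = t(0.975; 46) × √(2/24) = 2.013 × 0.289 = 0.58 SD. If the severity spread is added to the outcome SD at d = 1 (factor √(1 + p(1−p)), with p the severe share, 0.2 to 0.5), this becomes 0.63 to 0.65.

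**4. Effect on the test.** Taking 0.58 SD as the half-width, shifts of 0.17 and 0.25 SD raise the false-positive chance to about 9% and 14% (noncentral t, 46 df), given that the gap has occurred.

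A simulation (K = 14 or 24; d = 0.5 to 1.5; 20,000 runs per setting) compared the unadjusted t test with a model that includes severity. A gap of at least 20 percentage points means at least 6 patients at these K.

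| | unadjusted | severity in model |
|---|---|---|
| Type I error, overall | 4.9–5.2% | 4.8–5.2% |
| Type I error, given gap ≥ 20 points | 6.8–16.7% | 4.0–5.6% |
| Power for a 0.8 SD juice effect, overall | 58–75% | 76–77% |
| Same, gap ≥ 20 points against juice | 12–59% | 72–74% |

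**5. What baseline adjustment and severity each add.** Let v = p(1−p)d². The week-2 variance is 1 + v. After adjusting for the baseline marker it is (1 + v) − (r + v)²/(1 + v). After adding severity it is 1 − r².

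- d = 1, p = 0.5 (v = 0.25), r = 0.3: 1.25 → 1.008 → 0.91. Baseline removes 19%; severity then removes a further 1 − 0.91/1.008 = 10%.
- d = 1, p = 0.2 (v = 0.16), r = 0.7: 1.16 → 0.522 → 0.51. Baseline removes 55%; severity then removes a further 2%.

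Over p = 0.2 to 0.5 and r = 0.3 to 0.7, the baseline marker removes 16–58% at d = 1 and 11–52% at d = 0.5. Severity then removes a further 2–10% and 1–3% of the residual variance.

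**The case against.** The strongest reply is that not stratifying on severity is no error. Randomisation protects the test on average, the confidence interval already allows for chance imbalance, and an SAP that is not shown could add covariates. The first two points stand: unadjusted type I error was 4.9–5.2% overall. The third stands in part. An SAP could add adjustment, but the protocol itself names the between-arm tests, and they take no covariate.

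Entry is also less open than it seems. Patients are in hospital, give written consent and must be able to drink the product. Some serious conditions bar entry, and transfer to intensive care ends participation. This may narrow the severity range and favour the 0.5 SD case, where the effects are small.

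Four stronger readings are tempting, and the documents do not support them:

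- **An imbalance could be neither seen nor adjusted for.** Baseline CRP, ESR, IL-6 and blood count are collected. They are a partial proxy for severity and can be tabulated and modelled.
- **Severity is the main determinant and would move every marker together.** The background says only that some severe patients show cytokine syndrome. It ranks no determinants and makes no such statement about blood-count parameters.
- **Adjusting for severity is worth 28–30 patients per arm instead of 24.** That follows from removing v/(1 + v) = 14–20% of variance at 1 SD, but only against a model without the baseline value. Beyond baseline adjustment the gain is 2–10%.
- **Severity must replace age as a stratification factor.** This gives up balance on age by design, and nothing in the protocol shows which of the two predicts the outcome better.

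**Conclusion.** The point holds as one of precision and of results conditional on the allocation that occurs. Allocation on gender and age alone, unrestricted severity among admitted patients, 24 per arm and an unadjusted comparison together leave chance gaps in severity or baseline inflammation uncorrected. For 10, 14 or 24 severe of 48, a gap of at least 4 has a 29–39% chance and of at least 6 a 7–15% chance. At an assumed 1 SD severity effect these gaps move the contrast by 0.17 and 0.25 SD, roughly 30% and 40% of the half-width (0.17/0.58 and 0.25/0.58). The allocation does not bias the comparison. The severe share, the severity effect and the correlations are assumptions, and at 0.5 SD the shifts are half as large.

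**What to change.** 1. In Data analysis, replace the unadjusted between-arm test for each week-2 marker by a linear model (ANCOVA, on the log scale if the marker is skewed). Adjust for the baseline value of that marker and for gender and age. This needs no new data and brings most of the gain.
2. In the assessments section, record oxygen need at entry (yes/no) from the chart, and name it in advance as a further covariate. This costs one chart item per patient and one degree of freedom. The expected extra gain is modest: about 2–10% of residual variance at 1 SD and 1–3% at 0.5 SD. The item also lets readers see directly whether the arms differ in severity.

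The first change can be made at any time before the data are unblinded, the second before the first patient enters. Changing the stratification factors is optional.

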### **Follow up:**

Subsequent follow-up is to detect and minimize the effects of the confounding factors, as well as to accurately carry out the intervention protocol and will be done by well-trained, committed researchers.

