## **Data analysis**

The data will be analyzed by SPSS software version 25. After examining the normality distribution of variables using Kolmogorov-Smirnov test, quantitative normal variables will be reported as mean $\pm$ standard deviation, quantitative non-normal variables will be reported as median IQR, and qualitative variables as number (percentage). Independent T Test and Mann Whitney test will be used to compare the mean of variables between two groups. Paired T test or Wilcoxon test will be used to analyses within groups means. P-Value <0.05 will be considered as statistically significant. If the patient refuses to continue the study for any reason, statistical methods (Intention-to-treat analysis) will be performed.

1. STEPS, W., *Section 3: guide to physical measurements (Step 2)*, 2008, Geneva.

[figure not shown]

**Figure 1:** Study Process Flow chart

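### The gender-and-age blocks are described as lying inside each treatment group, so balance between arms is not secured as written, and the planned group comparisons leave both factors out; if assignment is stratified and the factors are prognostic, those tests are conservative and forgo power.

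*Protocol*

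**What the plan says.** Under Participants & recruitment, the protocol plans for "48 patients with definitive diagnosis based on PCR test", who "are included in the study by availability sampling". Under Study Design & randomization: "Patients will be randomly divided into two groups of intervention (n=24), and placebo (n=24), by block random sampling method". The same sentence goes on to say that this method "randomizes participants into 4 different blocks in each group, based on gender and age". It gives no age cut-off and no block size.

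Under Data analysis, the between-group rule is: "Independent T Test and Mann Whitney test will be used to compare the mean of variables between two groups". The within-group rule is: "Paired T test or Wilcoxon test will be used to analyses within groups means". The threshold is: "P-Value <0.05 will be considered as statistically significant". None of these has a gender or age term.

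Confounding is mentioned only under Follow up, as a purpose of that activity: "Subsequent follow-up is to detect and minimize the effects of the confounding factors". That is not a statistical adjustment.

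**The concern.** There are two linked defects.

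**The description of the allocation.** Blocking works because each block receives both treatments in a fixed ratio. Four blocks inside a group of 24 are four subsets of 24/4 = 6 patients who already share a treatment, and forming them balances nothing between arms. The sentence may be meant to describe four gender-by-age strata, but it does not say that. Recruitment is by availability, so equal strata cannot be assumed either. As the text stands, both a stratified and an unstratified list could be defended from it.

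**The analysis.** When assignment is restricted on factors that predict the outcome, the treatment difference varies less from trial to trial than an unadjusted standard error assumes. Leaving the factors out keeps the between-stratum variance in the error term. With 24 patients per arm there is little precision to give away.

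**Working it through.** **Inputs from the protocol.** 48 patients, 24 per arm (24 + 24 = 48, consistent); four gender-by-age blocks; a two-sample t test or Mann-Whitney test; threshold 0.05, taken here as two-sided because the protocol does not say.

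**Assumptions, because the protocol gives no figure.** R2, the share of marker variance explained by the four strata, is varied from 0 to 0.4. The effect is 0.8 SD, with total SD set to 1. A block size of 4 is used where one is needed.

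**Plan's own figure.** The sample size of 48 cannot be reproduced, because no effect size, SD or power is stated. For scale, the difference detectable with 80% power is (1.96 + 0.84) × √(2/24) = 0.81 SD, which is why 0.8 SD is used below.

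**Step 1: type I error if the strata are balanced between arms.** The difference in means then has a true variance of (1 − R2) × 2/24, while the unadjusted test uses about 2/24. The actual two-sided error is therefore 2 × [1 − Φ(1.96/√(1 − R2))]. At R2 = 0.2, 1.96/√0.8 = 2.19, which gives 0.028.

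| R2 | Formula | Simulated t test, 6 per arm in each stratum | Simulated t test, permuted blocks of 4 |
|---|---|---|---|
| 0 | 0.050 | 0.046 | 0.050 |
| 0.05 | 0.044 | – | – |
| 0.1 | 0.039 | 0.034 | 0.040 |
| 0.2 | 0.028 | 0.026 | 0.030 |
| 0.3 | 0.019 | 0.017 | 0.022 |
| 0.4 | 0.011 | 0.013 | 0.014 |

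With 6 per arm in each stratum, the Mann-Whitney test behaves the same way (0.043 at R2 = 0, falling to 0.013 at 0.4). A test adjusted for stratum stays at 0.047 to 0.054. The permuted-block column lets stratum sizes vary at random, so the result does not depend on equal strata.

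**Step 2: type I error if assignment is 24/24 without stratification.** The simulated error is 0.048 to 0.051 at every R2. The unadjusted test keeps its level. The mean largest within-stratum imbalance is about 4.2 patients, against 1.2 with permuted blocks of 4.

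**Step 3: power at 0.8 SD (simulated).**

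| R2 | Stratified: unadjusted | Stratified: adjusted | Points forgone | Unstratified: unadjusted | Unstratified: adjusted |
|---|---|---|---|---|---|
| 0 | 0.78 | 0.78 | 0 | 0.78 | 0.75 |
| 0.1 | 0.78 | 0.81 | 3 | 0.77 | 0.79 |
| 0.2 | 0.79 | 0.86 | 7 | 0.77 | 0.83 |
| 0.3 | 0.81 | 0.90 | 9 | 0.77 | 0.88 |
| 0.4 | 0.82 | 0.93 | 11 | 0.77 | 0.92 |

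**Check on step 3.** In the stratified case the standardised effect is 0.8/√(2/24) = 2.77.

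- Unadjusted power is about Φ((2.77 − 2.01)/√(1 − R2)). At R2 = 0.2 this is Φ(0.85) = 0.80.
- The adjusted test has non-centrality 2.77/√(1 − R2) on 48 − 5 = 43 degrees of freedom. At R2 = 0.2 that is 3.10, giving power 0.86.
- The gap of about 6 points agrees with the simulated 7 to within about a point.

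**The case against.** **The two consequences need opposite premises.** A reader might infer that balance is not secured and that P values are therefore too large. The documents do not support both at once. If the strata are not balanced, the unadjusted test holds about 5%; it is conservative only if stratification works and the factors are prognostic. This objection stands, and the conclusion below is conditional for that reason.

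**R2 is not in the documents.** Nothing in the protocol says how much of CRP, ESR, IL-6 or blood-count variance gender and age group explain, and one value need not suit all markers. At R2 of 0.05 or less the effect on type I error is negligible. This stands too, and is why the range starts at 0.

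**Power is forgone, not reduced below a target.** Unadjusted power rises slightly with R2 in the stratified case, and the protocol states no power goal that could be missed. The loss is relative to a better analysis of the same data. This is correct.

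**The sentence may be poor wording for a sound list.** A reader might infer that the allocation itself is faulty. No list is shown, so the documents establish a defective description and no more.

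**Adjustment could be left to a statistical analysis plan.** This carries less weight. The protocol is not silent: it names the tests, and those tests omit the factors on which it says assignment is based.

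**Conclusion.** The point holds in conditional form. As written, the randomisation sentence does not secure gender and age balance between arms, and the named between-group tests ignore both factors.

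- **If assignment is stratified and the factors are prognostic,** the tests are conservative. Type I error falls from 5.0% at R2 = 0 to 2.8% at 0.2 and 1.1% at 0.4, and 3 to 11 points of power at 0.8 SD are forgone over R2 of 0.1 to 0.4.
- **If assignment is not stratified,** type I error stays near 5%. Power is still forgone when the factors are prognostic: 0.79 − 0.77 = 2 points at R2 = 0.1 and 0.92 − 0.77 = 15 points at 0.4.

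A reader might infer a raised false-positive rate or a biased comparison. Neither follows: no setting examined showed type I error materially above 5%, and the defect costs efficiency. The wording defect is certain. The size of the analysis defect rests on an assumed R2, so overall confidence is medium. The change is worth making but is not critical.

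**What to change.** 1. **Rewrite the randomisation sentence**, for example: *Patients are stratified by gender and age group (cut-off stated); within each stratum, permuted blocks containing both arms in equal number assign juice or placebo.*
2. **Check that the randomisation list matches that text**, and correct it only if it does not.
3. **Include the gender-by-age stratum in every between-group comparison**, through a linear model, or with the van Elteren test if a rank test is kept.

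**Cost.** The change needs one sentence, a check of the list and a few degrees of freedom. It needs no new data, since age and sex are already on the demographic questionnaire. If the factors explain nothing and assignment was not stratified, adjustment costs about 3 points of power (0.75 against 0.78); if it was stratified, it costs essentially none. Incomplete blocks may also leave the arms not exactly 24 and 24: in the simulation with blocks of 4 and randomly varying stratum sizes, an exact split occurred in about 44% of trials. The arm sizes should therefore be stated as targets.
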